**3. Aims/Hypothesis**

**3.1 Primary Aim**

The primary aim of this study is to determine if adequate vitamin D supplementation (2000-4000 IU of vitamin D_3_ daily, assessed by a serum 25OHD level of ≥75 nmol/L) and calcium supplementation (1200 mg daily) in vitamin D deficient individuals at high risk of type 2 diabetes improve:

- Insulin sensitivity (homeostasis model assessment of insulin resistance – HOMA-IR);
- Glucose-stimulated insulin secretion (insulinogenic index and deconvolution analysis of C-peptide levels after a glucose load);
- Beta-cell function (disposition index).

**Primary Hypothesis:** Combined treatment with VD and calcium will significantly improve the insulin sensitivity, glucose-stimulated insulin secretion and β-cell function of VD deficient men and women at high risk of type 2 diabetes compared with placebo.

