  - The deconvolution analysis of C-peptide levels after a glucose load. C-peptide is probably a better indicator of insulin secretion than insulin itself since the latter is subject to hepatic clearance. Pre-hepatic ISR will be calculated from deconvolution of peripheral plasma C-peptide levels using a two compartment mathematical model with standard parameters for C-peptide distribution and metabolism, as previously described using the Chronobiological Series Analyses software (iBridge Network, [www.iBridgeNetwork.org](http://www.iBridgeNetwork.org), University of Chicago) [58]. Use of standard parameters for C-peptide clearance and distribution has been shown to result in insulin secretion rates that differ in each subject by only 10-12% from those obtained with individual parameters and there is no systematic over- or underestimation of insulin secretion. Incremental ISR from baseline during the first 30 minutes divided by incremental glucose and absolute total area under the curve of C-peptide by deconvolution analysis will be compared between baseline and 6 months of treatment.
- **Insulin resistance** will also be assessed by two methods:
  - The homeostasis model assessment for insulin resistance (HOMA-IR) is particularly suitable for obese and/or glucose intolerant subjects and has been shown to highly correlate with measures of insulin sensitivity obtained from the gold-standard procedure (euglycemic clamp technique) [59-61]. It is calculated from fasting insulin and glucose levels as follows: [Fasting insulin (mU/L) X fasting glucose (mmol/L)] ÷ 22.5.
  - Insulin resistance will also be estimated with the revised Quicki index: 1/[log (fasting glucose in mg/dl) + log (fasting insulin in μunits/ml) + log (fasting FFA). This index was shown to better correlate with euglycemic clamp than HOMA-IR in impaired glucose tolerant individuals (r=0,802) [62].
- **Beta-cell function** will be estimated by calculating the disposition index (DI): DI = insulin sensitivity (HOMA-IR) X ISR (deconvolution analysis of C-peptides).

*Evaluation of compliance*

Pill count will be performed after two months and at the end of the study to verify compliance to medication. Participants will be asked to report any change in their medication since the last visit.

*Monitoring of side effects and Safety Issues*

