**5.6 Statistical analyses**

Analyses will be performed using SPSS version 15.0. Skewed data will be log-transformed or examined using non-parametric tests. Differences in delta HOMA-IR between the treatment and the placebo group will be compared by two-sample unpaired *t* test. The change in DI and in ISR (assessed by deconvolution analysis of C-peptide levels and the insulinogenic index) and also the total area under the curve of C-peptide by deconvolution analysis will be compared between groups with unpaired *t* test. Analyses will be performed to assess changes in inflammatory markers, intact osteocalcin, adiponectin, blood pressure, lipid profile, FFA and weight with a two-sample unpaired *t* test. A *P*-value of ≤0.05 will be considered statistically significant. The endpoints will be adjusted for risk factors of type 2 diabetes: age, sex, BMI, family history of type 2 diabetes and physical activity. The following covariates will also be adjusted for: sunlight exposure and VD and calcium intake. Finally, the variables that predict response to treatment will be identified with multiple linear regression analyses. We will perform data analysis on an intention-to-treat principle. We will also perform analysis on patients who achieved >75% compliance with study medication as well as those on active treatment who achieved target 25OHD levels ≥75 nmol/L.

*Sample size calculation*

Sample size calculation is based on the difference in delta HOMA-IR [0.15 ± 0.18 (SD)] observed in a similar population of overweight subjects with pre-diabetes before and after a mean weight loss of 9.8 kg [64]. This change in HOMA-IR resulted in improved beta-cell function and reduction in the area under glucose curve during OGTT. This change in HOMA-IR was therefore considered clinically significant and was chosen for sample size calculation. A sample of 32 participants in each group will have 90% power to detect a difference in delta HOMA-IR of 0.15 with a standard deviation of 0.18 and 2-sided alpha of 0.05. Assuming a drop out rate of 20%, we will study a total of 80 participants.

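### The disposition index, sole measure of the third primary aim, does not say which deconvolution summary of insulin secretion it uses, and the choice affects how much of a true change it can show.

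*Protocol*

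**What the plan says.** Section 3.1 lists three outcomes under the primary aim. The third is "Beta-cell function (disposition index", and no other measure of beta-cell function is given.

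Section 5.5 gives the formula: "DI = insulin sensitivity (HOMA-IR) X ISR (deconvolution analysis of C-peptides". It carries no time window, no glucose term, and no word on whether the rate is incremental, mean or total.

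The insulin secretion rate (ISR) is described a few lines earlier: "Pre-hepatic ISR will be calculated from deconvolution of peripheral plasma C-peptide levels". Section 5.5 then names two quantities to be taken from that calculation: "Incremental ISR from baseline during the first 30 minutes divided by incremental glucose and absolute total area under the curve of C-peptide by deconvolution analysis". The first is related to glucose and the second is not.

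Section 5.6 plans unpaired t tests for "The change in DI and in ISR (assessed by deconvolution analysis of C-peptide levels and the insulinogenic index", and then adds the total as a separate item: "and also the total area under the curve of C-peptide by deconvolution analysis will be compared between groups with unpaired".

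**The concern.** A disposition index is meant to express how strongly the beta cell responds to glucose, given the prevailing insulin sensitivity. Secretion responds to glucose and also lowers it. If treatment makes beta cells more responsive, glucose after the load falls, and the weaker stimulus pulls the secretion rate back down. Secretion per unit of glucose is largely protected from this loop. Total secretion is not, and it also carries a basal part that dilutes any change in the response to the load.

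The two summaries in section 5.5 therefore behave differently, and the formula for a primary-aim outcome leaves the choice between them open. At stake are reproducibility (the same data can give two indices) and, if the absolute total is chosen, sensitivity to a real effect.

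**Working it through.** **1. What the text permits.**

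- *Glucose-free reading.* The formula says only ISR by deconvolution, and ISR is obtained from C-peptide alone. Taken literally, no glucose enters.
- *Glucose-divided reading.* Section 5.5 introduces insulin secretion rate as something estimated by two methods, and the first, the insulinogenic index, is itself a ratio to glucose. Of the two deconvolution outputs, the one that carries the label ISR is "Incremental ISR from baseline during the first 30 minutes divided by incremental glucose". Section 5.6 lists the total area apart from ISR.

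Both readings are open. Nothing in sections 3.1, 5.5 or 5.6 settles it.

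**2. The plan's own figure.** The only sample-size calculation is for delta HOMA-IR (difference 0.15, SD 0.18, two-sided alpha 0.05, 90% power). The normal approximation is 2 × (1.960 + 1.282)² × 0.18² / 0.15² = 30.3, so 31 per group. With the noncentral t, power is 0.898 at 31 and 0.907 at 32, so the stated 32 reproduces. 64 / 0.80 = 80 also reproduces. No power is stated for the disposition index, so this point does not touch the planned 80.

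**3. Direction of the effect, simple feedback model (assumed).** Let incremental glucose be G = A − kS and incremental secretion S = βG, with loop gain L = kβ. Then S = βA / (1 + L). If β rises by 20%:

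- S/G changes by the full factor 1.2, by construction.
- S changes by 1.2(1 + L) / (1 + 1.2L). For L = 0.5 this is 1.2 × 1.5 / 1.6 = 1.125, so 0.125 / 0.20 = 0.62 of the change is seen.
- If a basal share b of total secretion does not change, the fraction seen in the total is (1 − b) times that.

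| Assumed L | Fraction seen, incremental S without glucose | Fraction seen, absolute total, b = 0.30 |
|---|---|---|
| 0 | 1.00 | 0.70 |
| 0.1 | 0.89 | 0.62 |
| 0.25 | 0.77 | 0.54 |
| 0.5 | 0.62 | 0.44 |
| 1 | 0.45 | 0.32 |
| 2 | 0.29 | 0.21 |

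The protocol gives neither L nor b.

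**4. Size, illustrative 120-minute closed-loop model.** Assumptions, none from the protocol: basal glucose 5.8 mmol/L, fasting insulin 12 mU/L, secretion proportional to glucose above 4.5 mmol/L, insulin action varied four-fold, and 1/HOMA-IR as the sensitivity term in every version. After a true 25% gain in responsiveness:

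| Secretion factor | Change in the index |
|---|---|
| Absolute 120-min total | about +5% |
| Early (0–30 min) incremental ISR, no glucose division | +14 to +19% |
| Early incremental ISR divided by incremental glucose | +14 to +23% |

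Comparing like ends of the ranges, moving from the total to the early window recovers 14 − 5 = 9 to 19 − 5 = 14 percentage points. Dividing by glucose then adds 14 − 14 = 0 to 23 − 19 = 4. Other settings for absorption, clearance and insulin delay gave +5 to +6% for the total and +13 to +24% for the glucose-divided version; in one of them the undivided early rate gave +13 to +16% against +15 to +24%. The order of the summaries was stable; the sizes were not. The early window loses comparatively little because feedback has had less time to act, which corresponds to the low-L rows above.

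**5. The other factor.** Step 4 uses 1/HOMA-IR, but the written formula multiplies by HOMA-IR, defined as "Fasting insulin (mU/L) X fasting glucose (mmol/L)] ÷ 22.5", which rises with resistance. With β +20%, HOMA-IR −20% and L = 0.5 (and ignoring any effect of the HOMA-IR change on secretion):

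- 1/HOMA-IR × glucose-divided ISR: 1.2 / 0.8 = 1.50, a rise of 50%.
- As written, glucose-divided ISR: 0.8 × 1.2 = 0.96, a fall of 4%.
- As written, ISR not related to glucose: 0.8 × 1.125 = 0.90, a fall of 10%.

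This is a separate fault in the same line. Correcting it does not settle the secretion factor: with 1/HOMA-IR and an undivided ISR the rise is 1.125 / 0.8 = 1.406, that is 41% rather than 50%.

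**The case against.** A reader might infer that the secretion factor is plainly free of glucose, and that the index therefore shows only a fraction of any true change. The protocol does not support that. Its own labels attach ISR to glucose-related quantities and keep the total area separate, so the glucose-divided reading may even be the more natural one. Under that reading this source of attenuation disappears. No passage puts a 120-minute total into the index.

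The size is also open to challenge. Comparing a 120-minute absolute total with an early glucose-divided rate changes the time window, the basal share and the glucose division together, and most of the gap comes from the first two. The models set secretion proportional to glucose, so dividing by glucose recovers the change almost by design. They use 1/HOMA-IR, so a shift towards no effect does not describe the formula as written, which can change sign.

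Finally, glucose-related secretion is also analysed in its own right, and a statistical analysis plan, not shown here, could name the variable.

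Most of this stands against the stronger reading. It does not remove the ambiguity. The protocol chose to state the formula of a primary-aim outcome, stated it incompletely, and offers two candidates beside it. The separate secretion outcomes do not replace the only measure of beta-cell function.

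**Conclusion.** The point holds as one of incomplete definition. The secretion factor of the disposition index is not fixed, and the available choices do not perform alike. If the absolute 120-minute total were used, much of a true gain in responsiveness would be hidden: about +5% against about +14 to +23% for a 25% gain, under assumed feedback and with 1/HOMA-IR. An early incremental rate without glucose division loses comparatively little. The direction follows whenever secretion lowers glucose and glucose drives secretion; the size rests on assumptions that the protocol cannot confirm.

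It would go too far to say that the planned index is not related to glucose, or to attach a definite percentage loss to it. The sample size is unaffected. The definition should nevertheless be settled before the data are analysed, because the outcome belongs to the primary aim.

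**What to change.** In section 5.5, state that the secretion factor of the disposition index is the early summary already defined there: the rise in deconvolved secretion over the first 30 minutes per unit rise in glucose over the same interval. Multiply it by a true sensitivity term, for example 1/HOMA-IR. In section 5.6, refer to that single index, and show any product with the absolute total as descriptive only.

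The cost is a line or two of text. The glucose, insulin and C-peptide samples at 0, 10, 20 and 30 minutes are already scheduled, and the planned 80 participants do not change. The downside is that a ratio with a glucose increment in the denominator is noisier than a total.

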**5.6 Statistical analyses**

Analyses will be performed using SPSS version 15.0. Skewed data will be log-transformed or examined using non-parametric tests. Differences in delta HOMA-IR between the treatment and the placebo group will be compared by two-sample unpaired *t* test. The change in DI and in ISR (assessed by deconvolution analysis of C-peptide levels and the insulinogenic index) and also the total area under the curve of C-peptide by deconvolution analysis will be compared between groups with unpaired *t* test. Analyses will be performed to assess changes in inflammatory markers, intact osteocalcin, adiponectin, blood pressure, lipid profile, FFA and weight with a two-sample unpaired *t* test. A *P*-value of ≤0.05 will be considered statistically significant. The endpoints will be adjusted for risk factors of type 2 diabetes: age, sex, BMI, family history of type 2 diabetes and physical activity. The following covariates will also be adjusted for: sunlight exposure and VD and calcium intake. Finally, the variables that predict response to treatment will be identified with multiple linear regression analyses. We will perform data analysis on an intention-to-treat principle. We will also perform analysis on patients who achieved >75% compliance with study medication as well as those on active treatment who achieved target 25OHD levels ≥75 nmol/L.

*Sample size calculation*

Sample size calculation is based on the difference in delta HOMA-IR [0.15 ± 0.18 (SD)] observed in a similar population of overweight subjects with pre-diabetes before and after a mean weight loss of 9.8 kg [64]. This change in HOMA-IR resulted in improved beta-cell function and reduction in the area under glucose curve during OGTT. This change in HOMA-IR was therefore considered clinically significant and was chosen for sample size calculation. A sample of 32 participants in each group will have 90% power to detect a difference in delta HOMA-IR of 0.15 with a standard deviation of 0.18 and 2-sided alpha of 0.05. Assuming a drop out rate of 20%, we will study a total of 80 participants.

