**5.2 Randomisation and Intervention**

The proposed study is a prospective, double blind, randomised and placebo controlled 6-month clinical trial. Subjects will be randomly assigned to one of two groups, with stratification according to sex, age (< or >50 years of age) and BMI (< or >30). The treatment group will receive vitamin D_3_ (cholecalciferol) 2000 IU plus calcium carbonate (1200 mg elemental Ca daily) and the control group will take placebo pills. Permuted blocks of 4 treatment allocations will be used to ensure that after each 4^th^ allocation there are equal numbers in each treatment arm. After 8 weeks of treatment, if subjects in the treatment group have 25OHD levels less than 75 nmol/L, the dose of cholecalciferol will be increased to 4000 IU daily to reach optimal levels. On the other hand, subjects in the placebo group and those in the treatment group that reached optimal levels of 25OHD will be given extra placebo pills. To ensure blinding is respected, a person external to the study will look at the 8-week 25OHD results and contact patients to add an extra cholecalciferol or placebo pill to their regime, as appropriate.

The dosage of cholecalciferol has been estimated from the study of Barger-Lux and al., a rigorous trial performed in healthy overweight men [52]. They showed that each mcg (40 IU) of vitamin D_3_ increase the 25OHD concentration by 0.70 nmol/L. Based on the mean 25OHD level reported in populations of obese vitamin D deficient subjects (30 nmol/L) [25, 50, 53] and the expected increment described previously, it can be estimated that 2400 IU daily of vitamin D_3_ would be needed to increase the mean 25OHD level of our population to over 75 nmol/L. Of note, the dose-response relationship was not affected by body weight or fat mass. However, other data suggest that vitamin D requirements might be higher in obese compared to normal weight subjects [54]. Therefore, given that participants in our study will be obese, if adequate 25OHD levels are not reached after 8 weeks, the dose of cholecalciferol will be increased to 4000 IU daily. This dose, given daily for 3 months to 28 healthy adults, increased mean 25OHD levels from 37.9 ± 13.4 nmol/L to 96.4 ± 14.6 nmol/L [55]. None of the subjects had 25OHD levels <75 nmol/L at the end of the study.

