**5.8 Potential sources of bias**

The main factors that could affect insulin sensitivity, and consequently, insulin secretion are physical activity and weight change. Physical activity will be evaluated with questionnaires at the beginning and at the end of the study. This factor will be taken into account in the analyses. However, some data suggest that calcium supplementation could induce weight loss [65, 66]. If significant weight loss is observed between the treatment and placebo group, it will be difficult to discriminate the beneficial effects of calcium and vitamin D on insulin sensitivity and secretion from those induced by weight loss. However, this will be adjusted for in multivariate analysis.

Seasonal variation can influence endogenous 25OHD production. With small number block randomisation, this effect will be minimised by distributing patients equally between treatment groups within a small time frame.

1. Dunstan, D.W., et al., *The rising prevalence of diabetes and impaired glucose tolerance: the Australian Diabetes, Obesity and Lifestyle Study.* Diabetes Care, 2002. **25**(5): p. 829-34.
2. Cameron, A.J., et al., *Overweight and obesity in Australia: the 1999-2000 Australian Diabetes, Obesity and Lifestyle Study (AusDiab).* Med J Aust, 2003. **178**(9): p. 427-32.
3. Giulietti, A., et al., *Monocytes from type 2 diabetic patients have a pro-inflammatory profile. 1,25-Dihydroxyvitamin D(3) works as anti-inflammatory.* Diabetes Res Clin Pract, 2007. **77**(1): p. 47-57.
4. Targher, G., et al., *Serum 25-hydroxyvitamin D3 concentrations and carotid artery intima-media thickness among type 2 diabetic patients.* Clin Endocrinol (Oxf), 2006. **65**(5): p. 593-7.
5. Cigolini, M., et al., *Serum 25-hydroxyvitamin D3 concentrations and prevalence of cardiovascular disease among type 2 diabetic patients.* Diabetes Care, 2006. **29**(3): p. 722-4.
6. Li, Y.C., et al., *1,25-Dihydroxyvitamin D(3) is a negative endocrine regulator of the renin-angiotensin system.* J Clin Invest, 2002. **110**(2): p. 229-38.
7. Billaudel, B., L. Barakat, and A. Faure-Dussert, *Vitamin D3 deficiency and alterations of glucose metabolism in rat endocrine pancreas.* Diabetes Metab, 1998. **24**(4): p. 344-50.
8. Tanaka, Y., et al., *Effect of vitamin D3 on the pancreatic secretion of insulin and somatostatin.* Acta Endocrinol (Copenh), 1984. **105**(4): p. 528-33.

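### The endpoints are tested on change without adjustment for their own baseline, and the protocol does not say whether the t test or the adjusted analysis decides

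*Protocol*

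**What the plan says.** **Primary comparison (Protocol 5.6).** "Differences in delta HOMA-IR between the treatment and the placebo group will be compared by two-sample unpaired" t test. The same section applies an unpaired t test to the changes in DI, ISR and C-peptide area, and to the inflammatory, hormonal, blood pressure, lipid, FFA and weight outcomes.

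**Adjustment (5.6).** After setting the significance level at 0.05, the section continues: "The endpoints will be adjusted for risk factors of type 2 diabetes: age, sex, BMI, family history of type 2 diabetes and physical activity". It adds: "The following covariates will also be adjusted for: sunlight exposure and VD and calcium intake". That makes eight factors. Baseline HOMA-IR is not among them, nor is the baseline of any other outcome except, through BMI, body weight.

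**Skewness (5.6).** "Skewed data will be log-transformed or examined using non-parametric tests".

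**Sample size (5.6).** 32 per group gives "90% power to detect a difference in delta HOMA-IR of 0.15" with SD 0.18 and two-sided alpha 0.05. With 20% dropout the total is 80.

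**Randomisation (5.2).** Permuted blocks of 4, "with stratification according to sex, age (< or >50 years of age) and BMI (< or >30").

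**Season (5.8).** "With small number block randomisation, this effect will be minimised by distributing patients equally between treatment groups within a small time frame".

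**The concern.** A t test on change subtracts the whole baseline value, whatever its correlation with the 6-month value. ANCOVA estimates how much of the baseline to subtract, so in large samples its variance is never higher. It also removes chance baseline imbalance from the estimate, which matters with about 64 evaluable participants. The protocol collects baseline HOMA-IR for everyone but uses it only through the difference.

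The second issue is which result counts. Section 5.6 describes two analyses of the same endpoints under one significance threshold and ranks neither. If they fall on opposite sides of 0.05, the protocol does not say what the trial has shown. The ranking matters more because physical activity, sunlight and dietary intake are recorded both at baseline and at the end (5.5), and 5.6 does not say which measurement enters the model.

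A smaller issue is section 5.8's reliance on small blocks to balance season. Blocks are filled within strata, so they may fill too slowly to do this well.

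**Working it through.** **1. Reproduce the plan's own figure.** Inputs from 5.6: difference 0.15, SD of change 0.18, two-sided alpha 0.05, power 90%.

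- Standardised difference: 0.15 / 0.18 = 0.833.
- Noncentral t solution: 31.25, so 32 per arm (the normal approximation gives 31).
- Power at 32 per arm: 90.7%.
- Dropout: 64 / 0.80 = 80.

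The stated sample size reproduces for the unadjusted t test on change.

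**2. Effect of adding baseline.** Assume equal variance s² at both visits and baseline-to-6-month correlation r.

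- Variance of change: 2s²(1 − r).
- ANCOVA residual variance: s²(1 − r²).
- Ratio: (1 − r²) / [2(1 − r)] = (1 + r)/2.
- Adjusted SD on the protocol's scale: 0.18 × √[(1 + r)/2].

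The protocol does not give r, so a range is shown:

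| r (assumed) | Variance ratio | SD | Power at 32 per arm | n per arm for 90% |
|---|---|---|---|---|
| t test on change | 1 | 0.180 | 90.7% | 32 |
| 0.9 | 0.95 | 0.175 | 92.0% | 30 |
| 0.8 | 0.90 | 0.171 | 93.3% | 29 |
| 0.7 | 0.85 | 0.166 | 94.5% | 27 |
| 0.5 | 0.75 | 0.156 | 96.6% | 24 |

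These figures ignore the few degrees of freedom spent on covariates. They apply to raw HOMA-IR only, because the protocol gives no log-scale effect or SD.

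**3. Which factors each analysis contains.**

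| Factor | t test | Adjusted analysis |
|---|---|---|
| Sex, age, BMI (stratification factors) | no | yes |
| Family history, physical activity | no | yes |
| Sunlight, vitamin D and calcium intake | no | yes |
| Outcome's own baseline as a covariate | no | no |
| Season of randomisation | no | no (sunlight is a partial proxy) |

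**4. Season.** Three binary factors give 2 × 2 × 2 = 8 strata, and 80 / 8 = 10 participants per stratum on average, or two and a half blocks. The protocol states no accrual period, so 12 to 24 months of uniform accrual is assumed. In simulation with a cosine seasonal covariate:

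- A block takes a median of about 2 to 6 months to fill.
- The variance of the between-arm seasonal imbalance is 51–86% of that under complete randomisation. Unequal stratum sizes can lower the bottom of that range to about 41%.
- Unstratified blocks of 4 would leave 1–6%.

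**The case against.** **The stratification factors are not ignored.** A reader might infer from the t test that they are. Section 5.6 does not support that, since age, sex and BMI are all in the adjusted analysis. What stands is that the t test omits them and that the status of the adjusted analysis is unstated.

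**The planned test works.** It meets its 90% target and its sample size reproduces. The gain is about 1 to 6 percentage points of power, and a strongly correlated baseline (r of 0.8 to 0.9) yields only the lower part of that. This stands: the point is efficiency and clarity, not an invalid test.

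**An unseen SAP may rank the analyses.** It may, and the sample size is tied to the unadjusted comparison, which hints at an answer. But the protocol states both analyses as plans for the same endpoints, so it should itself say which is primary.

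**The skewness rule is workable.** One might infer that it cannot be applied to change scores, which can be negative. The documents do not support that: the rule allows rank tests, which accept negative values, and nothing rules out logging each visit's value before differencing.

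**Season is partly addressed.** Sunlight exposure is a covariate, and 5.8 claims only to minimise the effect. Blocking reduced imbalance in every simulated scenario. Any residue is chance imbalance, so a reading that the randomised comparison is biased by season is not supported. The protocol gives no effect of season on HOMA-IR, so the consequence for the primary result cannot be sized.

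**Conclusion.** The point holds in two parts. First, the outcome's own baseline is in neither the t test nor the covariate lists. Adding it cuts residual variance by 5–25%, which is worth 2 to 8 participants per arm at 90% power. That rests on an assumed r of 0.9 to 0.5, equal variances at the two visits, and the protocol's raw-scale SD of 0.18. Second, the protocol sets out an unadjusted and an adjusted analysis without saying which decides.

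The season statement in 5.8 promises more than stratified blocks are likely to deliver. That is a matter of wording and precision, and it depends on an assumed accrual period. None of this threatens the validity of the randomised comparison; the changes are worthwhile because they are nearly free.

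**What to change.** **In 5.6:**

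- Name one primary analysis: ANCOVA of 6-month HOMA-IR on treatment, baseline HOMA-IR, sex, age and BMI, reported with a 95% confidence interval.
- If HOMA-IR is to be logged, log each visit's value before modelling and say so in advance.
- Use the same form for DI, ISR and the secondary outcomes, each with its own baseline.
- Make the t test on change and the longer covariate list supportive, and state that covariates enter at their baseline values.

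**In 5.8:** say that stratified blocks give only partial seasonal balance. Season of randomisation, known from visit dates, can be added as a covariate.

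**Cost:** on the raw scale, wording only. All variables are already collected, and 32 per arm remains sufficient on the protocol's inputs. If the primary model is on the log scale, the sample-size paragraph also needs a log-scale effect and SD, which the protocol does not contain.
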